## Abstract

**Background:**

There are international concerns in relation to the management of patient deterioration which has led to a body of evidence known as the ‘failure to rescue’ literature. Nursing staff are known to miss cues of deterioration and often fail to call for assistance. Medical Emergency Teams (Rapid Response Teams) do improve the management of acutely deteriorating patients, but first responders need the requisite skills to impact on patient safety.

**Methods/design:**

In this study we aim to address these issues in a mixed methods interventional trial with the objective of measuring and comparing the cost and clinical impact of face-to-face and web-based simulation programs on the management of patient deterioration and related patient outcomes. The education programs, known as ‘FIRST^2^ACT’, have been found to have an impact on education and will be tested in four hospitals in the State of Victoria, Australia. Nursing staff will be trained in primary (the first 8 min) responses to emergencies in two medical wards using a face-to-face approach and in two medical wards using a web-based version FIRST^2^ACTWeb. The impact of these interventions will be determined through quantitative and qualitative approaches, cost analyses and patient notes review (time series analyses) to measure quality of care and patient outcomes.

**Discussion:**

In this 18 month study it is hypothesised that both simulation programs will improve the detection and management of deteriorating patients but that the web-based program will have lower total costs. The study will also add to our overall understanding of the utility of simulation approaches in the preparation of nurses working in hospital wards. (ACTRN12616000468426, retrospectively registered 8.4.2016).

## Background

The quality of patient care and patient safety are organisational, individual, and international responsibilities that require an appreciation of adverse events and medical errors [1–3]. In Australia, the Australian Commission on Safety and Quality in Healthcare has prescribed national standards with the objective of improving the quality of clinical care [4]. Health service providers are required to report compliance with these standards, including recognition and response to patients’ ‘severe clinical deterioration’ which is listed as Standard 9 – ‘Clinical Deterioration in Acute Health Care’ [5]. Thus, a key responsibility of providers of acute hospital care, and elsewhere, is to ensure that systems are in place to enable patients with severe clinical deterioration to receive immediate and appropriate assistance [6]. This includes the empowerment of clinicians to activate a ‘Medical Emergency Team’ (MET) (also known as a ‘Rapid Response Team’) whose members are skilled in the management of medical emergencies [7, 8].

Definitions of what constitutes a deteriorating patient or clinical deterioration are lacking, [9, 10] however there is a considerable body of evidence from the ‘failure to rescue’ literature indicating that the management of deterioration can be improved. This includes disturbed physiological variables in the general ward population [11], poorer patient outcomes for mismanaged patient deterioration [12–15], delays in team activation [16], missed indicators of deterioration in rural hospitals [14], a lack of knowledge as to when to call for assistance [17], and a failure to appreciate clinical urgency [18].

Efforts to improve recognition and response to clinical deterioration in Australia include the introduction of a National Patient Observation and Response Chart for recording of patient vital signs and observations [19]. Such standardised reports enable recording of core physiological observations as specified in the National Consensus Statement 1.6 (i.e. respiratory rate, oxygen saturation, heart rate, blood pressure, temperature and level of consciousness). Similarly, in the United Kingdom, physiological track and trigger systems are recommended to monitor all adult patients in acute hospital settings [20]. These charts utilise colour-coded graphed observation and vital sign documentation to designate the level of factors that should trigger an escalation of care. In Australia, the use of one of five available charts is mandatory except for the state of New South Wales where an alternative ‘Between the Flags’ - Standard Adult General Observation Chart is required in most public facilities [19, 21].

In relation to the management of emergencies it is known that the management of deteriorating patients can be enhanced through educative approaches [4, 5, 22–24] and through clinical and simulated experience [25, 26]. Education approaches emphasize the need for active learning in simulated environments that offer authentic learning experiences without risk to real patients [27, 28]. Clinical staff do benefit from simulation-based education in settings which have high fidelity (believability) [26, 29] with consequential reductions in medical errors [30].

This paper describes the protocol for a study that aims to address patient safety in relation to first responders’ ‘failure to rescue’ deteriorating patients, with a focus on enhancing the nursing assessment and management of clinical deterioration. Hospital registered nurse participants will be trained in the requisite primary responses to patient emergencies using two simulation approaches. Participants will participate in either in-situ face-to-face simulation or a web based simulation version of a valid clinical training package: FIRST^2^ACT (Feedback Incorporating Review and Simulation Techniques to Act on Clinical Trends) [31]. A cost benefit analyses will be performed and the clinical impact of training will be determined through a multi-method evaluation that will include quality of care evaluations, primarily achieved through pre-post intervention patient notes review with time series analyses.

## Methods/design

This multi-method study will utilize both qualitative and quantitative research techniques to evaluate the impact of FIRST^2^ACT on the quality of nursing care and patient outcomes. The design is a mixed methods interventional cohort trial comparing the impact of a web-based (Group 1) and face-to-face (Group 2) education program within and between groups.

### Aim and hypothesis

This research aims to measure the impact of two forms of simulation education on nurses’ ability to detect and manage patient deterioration, to assess patient outcomes and to compare the total costs between the two interventions. The research hypotheses to be tested are:(i).Both the face-to-face and web-based models of simulation education will improve the detection and management of patient deterioration and patient outcomes.(ii).The web-based program will have lower total costs in improving the detection and management of patient deterioration and patient outcomes.

The primary outcomes to be measured are the proportion of patients showing late clinical signs of deterioration, and the quality of nursing assessment. The secondary outcomes to be measured are the cost of provision of face-to-face versus web-based training, together with stakeholders’ views and attitudes regarding the forms of program delivery, and change to in-hospital mortality and the rate of admission to ICU (see Fig. 1).

**Fig. 1 Fig1:**
[figure not shown]
Logic model depicting research structure for the impact of web-based and face-to-face simulation on patient deterioration and patient safety

### Description of the intervention resource: FIRST^2^ACT

Face-to-face and web based versions of the FIRST^2^ACT program have been developed over the last eight years by some of the authors of this study (SC, RC, LK). The program has been widely reported with notable impacts on learning outcomes and a pilot study that measured the impact on clinical care [29, 32–36]. The web-hosted ‘e-simulation’ version FIRST^2^ACTWeb (see http://first2actweb.com/) (see Fig. 2) incorporates three interactive scenarios (myocardial infarction, shock and respiratory cases) where patient actors deteriorate (over eight minutes) with participants required to ‘click’ on various potential actions – such as measuring blood pressure or inserting an intravenous line - resulting in further pop-up videos of each action. Detailed performance feedback is then provided to a participant on completion [35]. The face-to-face version of the program (Fig. 3) mirrors the web based program (taking between 1.5–2 h to complete) and both include five key components: developing core knowledge; assessment (learning stimulus); simulation; reflective review; and performance feedback [31]. The initial development was funded by the Australian Office of Learning and Teaching from which a full project report is readily accessible [37].

**Fig. 2 Fig2:**
[figure not shown]
Group 1 - Screen shot of Web based version of First^2^Act interactive patient deterioration education program, depicting patient actor and action buttons

**Fig. 3 Fig3:**
[figure not shown]
Group 2 - Face-to-face simulation with patient actor during First^2^Act interactive patient deterioration education program

### Study status

This study commenced data collection in February 2016, to be completed by November 2016.

### Sample selection and recruitment

#### Participants

Registered nurses will be recruited from a medical ward in one of four Victorian acute care hospitals. Both Division 1 Registered nurses and Enrolled nurses will be included. Two medical wards will be assigned as Group 1 (web-based intervention), while another two will be assigned as Group 2 (face-to-face intervention). This approach ensures that there is no contamination between homogeneous groups. There are approximately 160 nurses employed at the larger hospitals and 85 at the remaining two sites. In pilot hospital-based studies we have achieved a participation rate of 82 % and anticipate similar participation for this study (*n* = >200). Maximising staff attendance is important in order to have the greatest effect on clinical outcomes.

Nurses in each group will be recruited by a member of the research team who will provide a brief explanation of the study and invite nurses to participate in the study. Participant information sheets and consent forms will be made available and written consent obtained.

#### Clinical impact measures

The impact of the interventions will be assessed on the proportion of patients that progress from early to late signs of deterioration and the quality of nursing care (primary measures). As per our previous studies we will use validated data extraction tools to mine data from patient observation charts. Appropriate frequency of vital signs and evidence-based responses to deterioration will be proxies for the quality of nursing care. Secondary measures include in-hospital mortality and admissions to ICU, and cost of provision of face-to-face versus web based education. We will also investigate stakeholder views and attitudes through semi-structured interviews with three key stakeholder groups at each site.

Patient sample size: Pilot data from an earlier rural study indicated that early signs of deterioration were present in 28 % of patients while late signs were present in 10 %, and that the total sample size required to detect a 5 % reduction in late signs of deterioration with a level of significance of 5 % and a power of 0.8 is 434 patients (217 before and 217 after the intervention) at each site [29].

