### Data analysis

Patient notes review: a pre-post intervention analysis through time series analyses. The appropriateness of observations, incidence of late signs of deterioration, in-hospital mortality and admissions to ICU will be used as the primary measures of patient management. Successful intervention will be identified by a statistically significant increase in applicable actions and a reduction in the proportion of late signs, in-hospital mortality and admissions to ICU.

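### The primary late-sign outcome is defined in two incompatible ways, and the stated sample size rests on one definition but does not give 80 % power for it

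*Protocol article*

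**What the plan says.** All references are to the protocol article.

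- **Aim and hypothesis:** "The primary outcomes to be measured are the proportion of patients showing late clinical signs of deterioration", alongside the quality of nursing assessment. No preceding early sign is required.
- **Clinical impact measures, opening sentence:** "The impact of the interventions will be assessed on the proportion of patients that progress from early to late signs of deterioration". This is labelled a primary measure. No denominator is named.
- **Data analysis:** the measure is the "incidence of late signs of deterioration", and success is judged partly by a statistically significant fall in late signs. Again there is no early-sign condition.
- **Clinical impact measures, patient sample size:** in the pilot "early signs of deterioration were present in 28 % of patients while late signs were present in 10" per cent. From this the article derives "the total sample size required to detect a 5 % reduction in late signs of deterioration" at 5 % significance and power 0.8: 434 patients per site, split 217 before and 217 after.
- **Patient medical records review:** 80 randomly selected cases a month for three months before and three months after, 480 per site, not restricted to patients with early signs. Table 2 lists early and late ranges for each parameter. For the Glasgow coma scale the early column is N/A and the late sign is a drop of more than 2 points.

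**The concern.** A patient who shows a late sign and a patient who moves from an early sign to a late one are not the same event. The article uses the first in two sections and in its sample-size inputs, and the second in the sentence that introduces the clinical outcome measures. Success depends on a significant reduction, so leaving both available means the quantity tested could be chosen after the data are seen.

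The patients on whom the definitions disagree also matter to this trial. Someone whose first charted abnormality is already late may be a case of missed deterioration, which is the problem the Background sets out. The progression definition leaves that patient out of the numerator.

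Finally, training is meant to change how often and how well nurses observe. A definition that depends on charted early signs can respond to charting alone.

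**Working it through.** **1. The two numerators.** The clearest case is a patient whose only Table 2 finding is a Glasgow coma scale drop of more than 2 points. Under Aim and hypothesis this patient is an event. Under the opening sentence of Clinical impact measures the patient cannot be one, because no early stage exists. A patient whose first abnormal reading is, say, an oxygen saturation below 90 % is treated the same way. This difference holds whatever the denominator. The article does not say how many such patients there are.

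**2. The denominator.** Patients with early signs is the natural reading of progression, but it is an inference. If it is right, charting matters. Illustration with 240 charts in a period, 24 with late signs (10 %), all also having early signs (assumption):

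- Early signs charted in 28 %: 240 × 0.28 = 67.2; 24 / 67.2 = 35.7 %.
- Early signs charted in 35 % (a value chosen for illustration): 240 × 0.35 = 84; 24 / 84 = 28.6 %.

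The progression proportion falls by about 7 points while the all-patient proportion stays at 10 % and no patient has fared differently.

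**3. The plan's own sample size.** Inputs: p1 = 0.10; p2 = 0.05 (the 5 % read as absolute, since a relative 5 %, 10 % to 9.5 %, would need 55,252 per period); two-sided alpha 0.05 (sidedness is not stated); power 0.80; equal periods.

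n per period = [1.960 × √(2 × 0.075 × 0.925) + 0.842 × √(0.10 × 0.90 + 0.05 × 0.95)]² / 0.05² = [0.730 + 0.312]² / 0.0025 ≈ 434.4, rounded up to 435.

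The article's 434 is therefore reproduced as the number needed in **each** period, or about 870 per site. No variant tried gives 217 per period: unpooled variance gives 432, arcsine 424, continuity correction 474 and a one-sided test 343.

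**4. Power of what is planned, all-patient definition.** Power = Φ{[0.05 × √n − 0.730] / 0.371}.

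| Charts per period | Two-sided | One-sided |
|---|---|---|
| 217 (stated) | 51 % | 63 % |
| 240 (80 × 3, planned) | 55 % | 67 % |
| 434 | 80 % | 88 % |

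**5. The same effect on the progression scale.** Suppose late-sign patients are nested in the 28 % (assumption). Then 10 % to 5 % of all patients becomes 10/28 = 35.7 % to 5/28 = 17.9 % of early-sign patients. This needs 96 early-sign patients per period, or 96 / 0.28 ≈ 343 charts. With 67 early-sign patients per period, power is about 65 % per site. If the pilot's early and late groups were instead disjoint (denominator 38 %), the change is 26.3 % to 13.2 %, which needs 143 patients (about 377 charts) per period. Power at 240 charts is then about 61 %.

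**The case against.** The best reply is that only one sentence is out of line. Data analysis agrees with Aim and hypothesis, the sample-size text points the same way, and exact numerators and observation windows are commonly left to a statistical analysis plan. That sentence also speaks of a proportion of patients, so its denominator may be all patients after all. Part of this stands: the weight of the text favours the all-patient definition, and the denominator conflict is inferred. The numerator conflict does not depend on it, however, and a later plan cannot agree with both stated primary measures.

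Four stronger readings are tempting and are not supported.

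- *The sample size is right for the all-patient definition and fails only for progression.* It is built on the all-patient inputs, but step 3 shows that 217 per period is about half of what they require.
- *Progression would be hopelessly underpowered.* A 5-point fall among early-sign patients (35.7 % to 30.7 %) has only about 9 % power per site, but the article specifies no such effect. For the planned effect and under nesting, progression has 65 % power against 55 % for the all-patient version.
- *The two definitions will move in opposite directions.* Step 2 shows one falling while the other stays still, no more. The all-patient outcome is not immune either: more frequent observation may reveal more late signs.
- *The pilot's 10 % is known to mean at least one Table 2 late sign.* The article does not say how the pilot counted late signs or over what period.

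It can also be said that two sites per program give 480 charts per period and about 84 % power for 10 % versus 5 %. That holds only if clustering by site is ignored, and the article states its requirement for each site.

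**Conclusion.** The concern holds. The article gives two primary late-sign outcomes that count different patients, and the conflict does not depend on the denominator. The sample-size inputs belong to the all-patient definition only. For that definition the stated 217 + 217 gives about 51 % power, and the planned 240 + 240 about 55 %, against the stated 80 %.

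These figures assume an absolute 5-point reduction, a two-sided test, independent charts and a simple before-after comparison of proportions at one site. A one-sided test raises them to 63 % and 67 %, still short. The progression figures (65 %, or 61 % with a 38 % denominator) also depend on how early and late signs overlapped in the pilot, which is not given. How far the two definitions would differ in the trial's own data cannot be computed from the article.

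**What to change.** Before analysis:

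1. State one primary definition, with numerator and denominator, in Aim and hypothesis, Clinical impact measures and Data analysis: the proportion of all sampled patients with at least one Table 2 late sign. This matches two of the three sections, the sample-size inputs and the unrestricted chart sampling.
2. Report progression from early signs as a secondary outcome outside the success rule, with its denominator named.
3. Correct the sample-size sentence so that 434 is a per-period figure, and restate power for the chosen definition at the planned 240 charts per period per site.
4. Note that more frequent observation after training may raise detected late signs, so that a null or adverse result is read with this in mind.

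The same charts are extracted under either definition, so the change is possible although data collection has begun. The cost is wording and a less favourable stated power. Restoring 80 % at each site would be a separate decision, at about 870 charts per site instead of 480.

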### Data collection tools

#### Patient medical records review

Using patients’ demography, diagnoses and vital signs data, outcomes will be measured in relation to deterioration including ICU admissions and mortality rates, etc. Further, based on our sample size calculations and the guidance produced by Harrison et al. [38], McQuillan [39] and NICE [40] we aim to identify a change in patient management by measuring the applicability of physiological observations, actions in relation to deterioration, and early and late signs of deterioration to identify improvements in performance (Table 2). We have developed and tested a chart audit tool based on a rationale for item inclusion, definitions, and clinical expert ratings of relevance and clarity with a high Content Validity Index of 0.83 [41]. We will therefore extract data from patient records from 80 randomly selected cases from each month, three months before the simulation intervention, and from each month for three months after the intervention (total *n* = 480 at each site). A post-hoc sensitivity analysis will be conducted to assess the representative nature of the sample.

**Table 2 Tab2:** Early and late signs of patient deterioration [Adapted from Harrison et al. [38]

Parameter	Early signs	Late signs
Oxygen saturation	90–95 %	<90 %
Systolic blood pressure (mmHg)	80–100 or 181–240	<80 or >240
Heart rate	40–49 or 121–140	<40 or >140
Respiratory rate	5–9 or 31–40	<5 or >40
Glasgow coma scale	N/A	>2 point drop

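### If training makes ward observations more frequent, more late signs will be charted, and the before-after reduction in late signs is biased towards no effect

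*Protocol article*

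**What the plan says.** All references are to the protocol article.

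- **Source.** Under Clinical impact measures, "we will use validated data extraction tools to mine data from patient observation charts".
- **Primary measures.** The same section names two: the proportion of patients who progress from early to late signs, and the quality of nursing care. For the second, "Appropriate frequency of vital signs and evidence-based responses to deterioration will be proxies for the quality of nursing care". Aim and hypothesis describes the first more simply, as the proportion of patients showing late signs.
- **Definition.** Table 2 under Patient medical records review ("Early and late signs of patient deterioration") gives threshold values, for example oxygen saturation below 90 % or systolic pressure below 80 or above 240 mmHg.
- **Hypothesis (i).** "Both the face-to-face and web-based models of simulation education will improve the detection and management of patient deterioration and patient outcomes".
- **Analysis.** Under Data analysis, "The appropriateness of observations, incidence of late signs of deterioration, in-hospital mortality and admissions to ICU will be used as the primary measures". The rule for success comes next in that section: "Successful intervention will be identified by a statistically significant increase in applicable actions and a reduction in the proportion of late signs"; the sentence goes on to list in-hospital mortality and ICU admissions.
- **Sensitivity analysis.** The only one named, under Patient medical records review, concerns how representative the sampled records are.

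**The concern.** A late sign that nobody measures or writes down is not counted. The training is intended to change how well nurses detect deterioration and how appropriately often they take vital signs, and it does so between the two periods being compared. If it works, patients after training have more observation sets, and each set is another chance for a threshold value to be recorded.

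The charted proportion therefore mixes two things: how often patients truly deteriorate, and how closely they are watched. For the simple proportion with late signs these pull in opposite directions. Better care should lower it; closer observation raises it. The success rule asks for improved actions and fewer late signs together, so success on one part works against the other.

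What is at stake is a false negative, or an apparent worsening, on a primary outcome that nobody could then interpret. A time series model of the charted proportion does not remove the problem by itself, because charting would change at the same time as the training.

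**Working it through.** **Inputs from the article.** Late signs 10 % and early signs 28 % at baseline (pilot data); a 5 % reduction, read as 10 % to 5 %; significance 5 %, taken as two-sided; planned records 80 per month for three months before and three after, so 80 × 3 = 240 per period per site. Two sites per program give 2 × 240 = 480 per period. That pooling is my reading of a program-level comparison; the article states its sample size per site.

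**The plan's own figure.** The pooled-variance formula for two proportions, 10 % against 5 %, 80 % power, two-sided, gives 435 per period. The article states 434 in total (217 + 217), so its figure does not reproduce as a total. That is a separate matter and nothing below rests on it. The reference powers used here are 55 % at 240 per period and 84 % at 480.

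**Assumption needed.** The article gives no observation density, so the increase in sets is assumed to be 25 % or 50 % (k = 1.25 or 1.5).

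**Step 1: charted rate.** If sets are independent, the chance of at least one late value with k times as many sets is 1 − (1 − p)^k.

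| True state after training | k = 1 | k = 1.25 | k = 1.5 |
|---|---|---|---|
| No change (p = 0.10) | 10.0 % | 12.3 % | 14.6 % |
| True halving (p = 0.05) | 5.0 % | 6.2 % | 7.4 % |

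Of the true 5-point reduction, 10 − 6.2 = 3.8 points (k = 1.25) or 10 − 7.4 = 2.6 points (k = 1.5) remain visible. About a quarter to a half is lost.

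**Step 2: power when late signs are truly halved.** Power = Φ[(d − 1.96·se0)/se1], where d is the difference, se0 the pooled and se1 the unpooled standard error. Example, n = 240 and k = 1.25: d = 0.0379, se0 = 0.0249, se1 = 0.0249, giving Φ(−0.44) = 33 %.

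| Per period | k = 1 | k = 1.25 | k = 1.5 |
|---|---|---|---|
| 240 (one site) | 55 % | 33 % | 17 % |
| 480 (two sites) | 84 % | 58 % | 30 % |

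**Step 3: a different model.** Let the charted rate be the true rate times the probability s that a late sign is charted, with the charted rate before training fixed at 10 %.

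- s from 0.7 to 0.9: the true rate before is 0.10/0.7 = 14.3 %. With no true effect the charted rate after is 0.143 × 0.9 = 12.9 %. With a true halving it is 0.0714 × 0.9 = 6.4 %, and power at 240 per period is 30 %.
- s from 0.9 to 1.0: 11.1 % with no effect, 5.6 % with a true halving, power 44 %.

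Both models give the same direction.

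**Step 4: progression from early to late signs.** Baseline is 10/28 = 35.7 %. Scaling both early and late signs by Step 1 gives 12.3/33.7 = 36.6 % (k = 1.25) and 14.6/38.9 = 37.6 % (k = 1.5), so it barely moves. If extra sets uncovered only early signs and late signs stayed at 10 %, it would fall to 10/33.7 = 29.7 % or 10/38.9 = 25.7 %. The direction depends on which signs the added sets reveal.

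**The case against.** **The article never says that observations will increase.** It speaks of appropriate frequency and applicable actions. That is correct, and a reader who infers that the success rule demands more observations goes further than the text. More frequent sets are an inference, but a fair one from a hypothesis of better detection in a setting where the article says cues are missed.

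**The counting rule may be defined elsewhere.** Table 2 gives thresholds only, and the chart audit tool, with its definitions, is not shown. A review window or counting rule could sit there and reduce the bias. The absence of an adjustment from a condensed article is not in itself the point. The point is that the data source, outcome, proxy and success rule which the article does fix are linked in this way.

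**The magnitude is assumed.** This stands. No set density is given, and independence overstates the effect of uniformly added sets because successive sets are correlated. On the other hand, extra sets aimed at the sickest patients could do more than the model shows.

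**A stronger reading does not hold.** A reader might infer that, on the progression measure, the bias reverses and a program that changes only charting could look effective. Progression falls clearly only if late signs are held fixed while early signs rise; scaling both leaves it almost unchanged. The success rule also lists mortality and ICU admissions, which do not depend on charting density in this way, so a charting-only change would not clearly meet it.

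**Conclusion.** The point holds as a bias towards no effect, of unknown size, on the simple before-after comparison of the proportion with late signs. It rests on one inference, that observation sets become more frequent after training, and on late signs being counted from whatever sets are charted.

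If sets rise by 25-50 % and are independent, a true halving would look like a fall from 10 % to 6.2-7.4 %, with the losses of power shown above; smaller or correlated increases would cost less. The documents establish neither a bias in favour of the program nor a definite direction for the progression measure. Mortality and ICU admissions are not affected by this mechanism. The matter deserves action because it touches a primary outcome and the success rule, and because a null or adverse late-sign result could not otherwise be explained.

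**What to change.** 1. Extract the time of every observation set when the charts are audited.
2. Report observation sets per patient-day, by period and site, beside the late-sign proportions.
3. Pre-specify a late-sign analysis at fixed sampling density alongside the all-sets analysis: for example, use only the first charted set in each nursing shift, and report by period the shifts with no charted set.
4. Interpret the late-sign result in the light of both analyses. Do not require them to agree as a condition of success: that would keep the biased version as a gate and add a less precise one, making a false negative more likely.

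**Cost.** One extra extracted item (assuming set times are legible on the charts), one derived variable and one further analysis; no extra patients. The thinned version counts fewer late signs and is less precise. It is only approximately neutral to density, because the number of shifts without any set may itself change with training.
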